## Abstract

**Introduction:**

An open dialogue between parents of children with cancer and medical staff about the benefits, risks, and interactions of complementary medicine used during cancer treatment is essential to enhance treatment safety and efficacy. However, both parents and medical staff often lack sufficient knowledge and willingness to engage in such discussions. To address this, bedside counseling for patients and families is proposed, provided directly by an external team comprising experienced specialists in complementary and conventional medicine. This approach aims to facilitate communication, improve understanding, and mitigate risks associated with complementary medicine during pediatric cancer care.

**Methods:**

This study will be conducted in five pediatric cancer centers in Germany. Physicians specializing in complementary medicine and pediatric oncology will provide bedside counseling to patients, parents, and local medical staff. Feasibility and change measures will be evaluated by comparing cohorts of parents who received complementary medicine counseling with those who did not, as well as medical staff before and after training sessions. Semi-structured interviews with parents and medical staff will further explore barriers to complementary medicine counseling and identify strategies to enhance its implementation. Quantitative data will be analyzed to assess the feasibility of the intervention, while qualitative data will provide in-depth insights into the perspectives and experiences of stakeholders.

**Results:**

The results will highlight predictors for effective, use-oriented counseling tailored to different target groups. This prototype support care model will serve as a framework for implementing complementary medicine counseling both within and beyond inpatient pediatric oncology settings. By integrating these findings, we aim to develop a replicable approach to complementary medicine counseling that addresses the unique needs of pediatric cancer patients, their families, and medical professionals.

**Discussion:**

Previous initiatives have primarily focused on training individual physicians within each center to address complementary medicine. In contrast, this novel strategy emphasizes direct bedside counseling for pediatric patients and families while providing ongoing support to local staff. This approach seeks to enhance treatment safety by reducing unintended interactions between complementary medicine and conventional cancer therapies, ultimately improving care quality and patient outcomes.

**Trial Registration:**

German Clinical Trials Register (DRKS), ID: DRKS00030478. Registered 22 December 2022 https://www.drks.de/DRKS00030478.

## Introduction

1

The terms “Complementary Medicine” (CM) and “Alternative Medicine (AM)” are often used interchangeably but do in fact represent different concepts. Alternative treatments are used instead of conventional therapies, while complementary therapies are used in addition to conventional therapies when the latter are needed (1). Both therapy concepts encompass a broad spectrum of pharmacological and non-pharmacological, traditional and non-mainstream approaches, although for decades AM was mainly offered outside a conventional medical setting (2). This often causes unintended interactions with conventional treatments, in particular in cancer patients, and probably negatively impacts disease progression (3–5). Integrative medicine (IM) is an approach to medical care that recognizes the benefit of combining conventional (standard) therapies with complementary therapies that have been shown to be safe and effective. It uses the best evidence available in terms of efficacy and safety and focuses on the person as a whole (6).

In recent years, the use of CM has increased worldwide and now the World Health Organization describes CM as an important and often underestimated part of health care (7). There is growing interest and use of CM for both adults (8) and children (9, 10), as well as in adult and pediatric cancer patients (11, 12). Reasons given for the use of CM include side-effect management, physical stabilization and strengthening of the immune system, as well as the need to do something “extra” by oneself (11, 13, 14).

It is also worth noting that attitudes toward CM among health care professionals have become increasingly positive, with greater interest in and acceptance of integrating CM into conventional medicine (8, 15, 16). The use of CM in pediatric oncology requires the applicable IM concepts. However, as research shows, it is still unclear which CM treatment is used at which stage of conventional pediatric cancer treatment (11, 17). Längler et al. (11) assume that information about CM therapies is given to parents from a variety of sources such as relatives, friends, alternative practitioners, pharmacies and many others. In addition, online media are currently the most commonly used sources of information by parents with a pre-existing interest in alternative therapeutic options when seeking information about CM (17, 18). This information is often poorly comprehensible, often pertains to adults rather than to children, and can in some cases even be harmful due to misinformation or inappropriate content for young audiences (19). A major problem is that only about 50% of parents inform their pediatric oncologist about their CM use (10) and, equally, treating oncologists often do not actively ask about the CM use of their patients because of insufficient knowledge about CM (11, 14, 20, 21). In summary, CM counseling and support is a severely neglected area of physician-patient communication (22).

Parents of pediatric cancer patients emphasize the need for evidence-based information about effects and risks of CM, and healthcare professionals call for training opportunities on the safe use of CM to prevent unintended interactions with conventional therapies (18). In recent years, there have been promising concepts for improving knowledge about the safe use of complementary medicine (CM) in pediatric cancer centers, such as offering voluntary training courses to pediatric oncologists. These training programs have been provided by expert groups and professional organizations, aiming to equip oncologists with the necessary skills to address CM-related concerns (23). However, a limitation of these programs is that they predominantly involve physicians with a pre-existing interest in CM, which may introduce bias and reduce the generalizability of the findings. Specifically, pediatric oncologists without prior knowledge of CM are often insufficiently reached, although they could benefit the most from such training (24). Moreover, many cancer centers in Germany do not employ specialists with expertise in both CM and pediatric oncology (25).

From a broader perspective, several studies have examined the sources of knowledge and perceptions about CM among both parents and medical staff. Parents often rely on a mix of personal experiences, internet sources, and anecdotal reports from other parents, while medical staff generally acquire their knowledge through specialized training programs, clinical experiences, and guidelines, such as the German AWMF guidelines on CM in oncology (26). Despite the availability of such resources, there remains a significant gap in the practical implementation of CM counseling in pediatric cancer settings, where many parents still turn to external sources for guidance. The current project addresses this gap by involving an external team of pediatric cancer specialists consisting of the authors of this study providing counseling expertise in complementary and conventional medicine, providing counseling and training to medical staff and parents at five pediatric cancer centers in the Rhine-Ruhr region of Germany. This collaborative, interdisciplinary approach ensures that families receive evidence-based CM advice directly from trained healthcare professionals, mitigating the risks associated with self-researched information and enhancing the overall safety of pediatric cancer care (23, 24).

## Objectives

2

The main objective of the study is to explore the feasibility and acceptability of implementing CM counseling and supporting strategies in conventional pediatric cancer centers without in-house specialized CM counseling services. Feasibility refers to the extent to which a new intervention, program, or procedure can be successfully delivered in a specific context that is not fully controlled. It involves assessing whether the implementation processes can be carried out as intended in real-world settings, considering various logistical, operational, and contextual factors (Berry & Shabana 2020). Throughout this manuscript, the term “medical staff” is used comprehensively to refer to a diverse group of professionals involved in the treatment and care of children. This includes not only physicians but also nurses, therapists, and social educators. The broad application of this term reflects the interdisciplinary nature of pediatric care, in which various professional groups collaborate to ensure holistic and effective treatment. Beside training of medical staff in the dos and don'ts of CM, personal counseling of parents is taking place directly at the patients' bedside about how they handle CM used in parallel with conventional treatment, what kind of CM is allowed, what they should omit and what is dangerous.

Acceptability, on the other hand, pertains to the extent to which the target population and stakeholders involved in the implementation perceive the intervention or procedure to be satisfactory, appropriate, and agreeable. This includes their comfort with, perceptions of, and reactions to the intervention, which can significantly influence its successful uptake and sustainability [Berry & Shabana, 2020; (27)]. This intervention will be scientifically evaluated in relation to the following acceptability criteria:.
1.What are the needs of parents of children with cancer and medical staff regarding counseling on the safe use of CM?2.Is the CM intervention that has been developed acceptable for the parents of children with cancer as well as for medical staff?The following feasibility issues are also central to the study:
1.Is it feasible to recruit a sufficient number of parents/medical staff to obtain representative cohorts?2.Is it feasible to implement CM interventions in different conventional study centers according to the protocol or are there barriers that will require protocol adjustments?Secondary objectives include exploratory outcomes for evaluation:
1.Do trained parents feel better informed about the risks, benefits and safety of CM compared to untrained parents, and does this increase their ability to make better informed decisions about their use of CM?2.Do attitudes towards CM and CM usage differ between trained and untrained parents?3.To what extent does the medical staff feel relieved from administrative tasks, time pressure, and professional uncertainty by the external provision of CM counseling for parents?4.Can knowledge of the benefits and risks of CM among medical staff and their attitudes towards it be improved?The results should make it possible to successfully implement and establish CM counseling and supporting strategies in conventional pediatric cancer centers. In addition, individual CM counseling concepts will be developed for other clinics in the long term, in order to meet evidence-based IM recommendations (6).

## Methods and analysis

3

The study protocol was drawn up according to the standard protocol items for clinical trials (SPIRIT) guideline (28) as well as Consolidated Standards of Reporting Trials (CONSORT) (29). Each study site was approved by the respective ethics committee and registered at the WHO International Clinical Trials Registry Platform/German Clinical Trials Register (DRKS00030478) before patient recruitment. The inclusion of patients and healthcare providers is essential in our study to integrate their perspectives into the research process. Their active involvement in developing survey instruments and pilot-testing study procedures ensured relevance and user-friendliness. Additionally, continuous feedback through a dedicated hotline and suggestion boxes allows for real-time adjustments and improvements to the study experience.

### Study setting and design

3.1

Several large centers for pediatric oncology and hematology are located in the Rhine-Ruhr area, with more than 30% of all pediatric cancer patients in Germany being treated in this region. The Gemeinschaftskrankenhaus Herdecke, Germany, is a pediatric oncology center according to the quality criteria of the Federal Joint Committee (Gemeinsamer Bundesausschuss, G-BA), a member of the Society for Pediatric Oncology and Hematology-network (Gesellschaft für Pädiatrische Onkologie und Hämatologie, GPOH) and the coordinating study center. Further participating centers are:
-Vestische Children's and Youth Hospital Datteln, Germany-Pediatric Hematology/Oncology, Dortmund Hospital, Germany-Department of Pediatrics and Adolescent Medicine, University Hospital Essen, Germany-Pediatric Hematology/Oncology, University Hospital Cologne, GermanyThe Rhine-Ruhr metropolitan area is beneficial for the fact that there are many oncological centers in a very small area, so that the treatment team can drive to them and deliver bedside counseling and support in presence. By selecting a prospective, multicenter study design, two cohorts of parents of children with a diagnosis of cancer and one cohort of medical staff from the participating pediatric oncology departments can be included. Sociodemographic data will be collected from all cohorts, with particular emphasis on the educational level of the parents, to determine whether education influences responses in the surveys. While one parent cohort will receive CM counseling, the other will serve as a waitlist cohort to be offered the respective CM counseling after the outcome assessment. Group assignment will be non-randomized by starting with a control cohort followed by the intervention cohort. After being informed about the study during the initial visit by their treating physician and signing written informed consent, parent cohorts will receive standard questionnaires three weeks after study inclusion. For the parent control cohort, the CM counseling will take place after this outcome assessment, while the parent intervention cohort will receive CM counseling before. Outcomes will be compared between groups. Medical staff will be trained in CM counseling strategies and assessed before and after the CM training. Outcomes will be compared within this group. A summary of the study design can be found in Figure 1. The active study period of recruiting is scheduled from December 2022 to end of 2027. Since there are five participating centers and a small project team, the time invested to be able to include subjects in the study will be in relation to the effort involved. For the medical staff, 100 participants are considered an acceptable and desirable number. Traveling to the study centers and maintaining contact with parents requires resources. The sample size for the survey and consultation includes 50 participants, evenly divided into two cohorts of 25 individuals each. We also expect a dropout of 10%, as parents who find themselves in such a difficult situation might also turn away.

**Figure 1 F1:**
[figure not shown]
Study flow chart with control and intervention group and an overview of processes that will run consecutively in each participating cancer centers individually.

### Eligibility criteria

3.2

To be included in the study, participating parents must have reached the age of 18. Their children should be under 18 years of age. Both parents have to give written informed consent to participate in the study. Children who have already reached the age of 16 must give their written consent as well. All first-onset oncological diseases are considered eligible diagnoses and the children have to be undergoing conventional cancer treatment in one of the participating cancer centers. Parents who already have experience in dealing with CM can still be part of the study.

Medical staff will be eligible if they are employed in one of the participating study centers within the framework of pediatric oncology and provide written informed consent. Insufficient knowledge of German is considered an exclusion criterion for both parents and medical staff.

### Selection and treatment of subjects

3.3

Parents and their children who meet the inclusion criteria are recruited at the participating study centers and made aware of the study during the initial visit with their treating on-site oncologist. Afterwards, enrolled pediatric patients and their parents will be informed by study staff about the nature, significance and scope of the study. They will also receive written confirmation that no disadvantages in medical treatment of their children will occur if they do not participate.

The medical staff will also be recruited at the participating study centers by the study team, who will inform pediatric oncologists and nurses about the study and hand out written study information. The collection of data will take place on site. If participants can no longer be reached on site, further data collection will be carried out by mail or online.

### Interventional methods

3.4

The intervention for parents will include a half-hour CM counseling session at the respective treatment center and, if necessary, an ongoing exchange. The personal counseling and support are planned to take place directly at the bedside and includes advice on how to safely use CM therapies in addition to conventional cancer therapy. In this setting, parents have the opportunity to ask questions of interest about CM. To ensure comprehensive reporting and implementation of the intervention, we will utilize the Template for Intervention Description and Replication (TiDier) framework (30). This framework will guide the detailed description of the intervention components, delivery methods, and the context in which it is implemented. Additionally, a fidelity checklist, informed by the GRIPP2 reporting framework, will be employed to assess the consistency and accuracy in delivering the intervention across different sites and facilitators (31).

The intervention for the medical staff will consist of frontal training units on the communication of CM topics mainly related to the effects, adverse events and interactions of different CM therapies with conventional cancer treatment. This is supplemented by case-based training in each of the five participating centers.

For the parent intervention cohort as well as the medical staff cohort, evidence-based information is made available on the SiKOM homepage (www.sikom.info) and by means of brochures for all those interested in further CM information. Moreover, study participants have the opportunity to ask questions or receive information on individual concerns via a telephone hotline, which is available throughout the entire duration of the project.

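### Section 3.4 opens the telephone hotline to study participants without a cohort limit, so waitlist parents may obtain individual CM information before their only questionnaire

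*Protocol article*

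**What the plan says.** Section 3.4 (Interventional methods) describes two supports beyond the bedside session. The first is tied to named cohorts: "For the parent intervention cohort as well as the medical staff cohort, evidence-based information is made available on the SiKOM homepage", together with brochures. The second comes in the next sentence and names no cohort: "study participants have the opportunity to ask questions or receive information on individual concerns via a telephone hotline". The line stays open for as long as the project runs.

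Section 3.1 (Study setting and design) sets the control condition. One parent cohort is counseled, while "the other will serve as a waitlist cohort to be offered the respective CM counseling after the outcome assessment". On timing, "parent cohorts will receive standard questionnaires three weeks after study inclusion", and "For the parent control cohort, the CM counseling will take place after this outcome assessment". Section 4 (Outcomes) gives each parent cohort a single questionnaire.

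Section 3 (Methods and analysis) mentions a hotline once more, as a feedback channel and again without a cohort limit: "continuous feedback through a dedicated hotline and suggestion boxes allows for real-time adjustments and improvements to the study experience".

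**The concern.** A waitlist comparison depends on the control cohort not receiving the active content before it is assessed. Parent counseling in 3.4 consists of individual advice on safe CM use, the chance to ask questions and, where needed, continuing exchange. A telephone line that answers questions on individual concerns overlaps with that content.

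The comparison at stake is counseled versus uncounseled parents on feeling informed, ability to decide and attitudes. Section 2 lists these among the secondary, exploratory objectives, and 4.3 names them among the hypotheses to be tested. Section 4.6 plans independent t-tests or Mann–Whitney tests between cohorts. If control parents were partly informed by telephone first, a small observed difference could reflect either weak counseling or an informed control cohort. With one questionnaire per parent, the parent's own data offer no earlier measurement that could help to tell these apart.

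**Working it through.** This is mainly a question of text, so the provisions are set side by side first. The article states no power, effect size or standard deviation, so there is no figure of its own to reproduce.

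**Who.** The homepage sentence in 3.4 names two cohorts. The hotline sentence names study participants only. Under 3.1, control parents have signed consent before the three-week interval starts, so the term covers them.

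**When.** The hotline runs for the whole project. Section 3.1 recruits the control cohort first, so the line is open during the control phase too. No sentence ties access to completion of the questionnaire.

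**What.** The hotline sentence covers questions and information on individual concerns, and it stands under the heading for the intervention. It does not use the word counseling. Section 3 describes the hotline as a route for feedback.

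**Result.** Section 3.1 withholds counseling from control parents until after the questionnaire, while 3.4 read literally gives them a route to overlapping content before it. No other section of the article restores the limit.

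**Direction and possible size (illustration only).** Let D be the true difference between counseled and uncounseled parents, c the share of control parents who obtain CM information by hotline before the questionnaire, and f the fraction of the counseling effect that a call delivers. The control mean moves by c × f × D, so the expected difference is D × (1 − c × f). Both c and f are assumptions.

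As a yardstick, take the difference that 25 parents per cohort would detect with 80% power. Assume a two-sided test at 0.05, since 4.6 gives the level but not the sidedness. By the normal approximation this is (1.960 + 0.842) × √(2/25) = 0.79 SD. After dilution to d, power is Φ(d/√(2/25) − 1.960). For c = 20% and f = 0.5, d = 0.792 × 0.90 = 0.713, then 0.713/0.2828 − 1.960 = 0.561, and Φ(0.561) = 71%.

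| c | f | Share of D remaining | Power, starting from 80% |
|---|---|---|---|
| 10% | 0.5 | 0.95 | 76% |
| 20% | 0.5 | 0.90 | 71% |
| 30% | 0.5 | 0.85 | 66% |
| 20% | 1 | 0.80 | 61% |
| 50% | 0.5 | 0.75 | 56% |
| 50% | 1 | 0.50 | 29% |

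With the 10% dropout in 3.1 (25 × 0.9 = 22.5, taken as 22 per cohort) the yardstick becomes (1.960 + 0.842) × √(2/22) = 0.84 SD. The power column is unchanged, because it is scaled to that yardstick.

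**The case against.** The strongest reply is that the paragraph in 3.4 opens with the intervention parents and staff, and the hotline sentence continues from there. The authors may have meant only those two cohorts. That reading is plausible and cannot be excluded, and the flow chart that might settle it is not shown. But the limit is absent from the very sentence that offers individual information, and a site working from the text could apply either reading.

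Second, the hotline may be largely organisational. Section 3 presents it as a feedback channel, and 5.2 mentions telephone feedback as a way to keep participants committed. This weakens any claim that the hotline is a named component of the intervention. It does not remove the wording in 3.4 on individual concerns.

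Third, the parent comparison is exploratory. Section 4.6 sets no formal sample size, and 5.1 says that the questionnaire outcomes only indicate a direction. This stands, and it limits the weight of the point.

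Fourth, the homepage address is printed in the article, so a cohort label alone may not keep control parents from general information. That is fair, but general material that a parent finds alone differs from an individual answer offered by the study team.

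A reader might infer more than the article supports:
- **That control parents do receive counseling by telephone.** The text shows possible access, not use.
- **That a particular loss of power follows.** Every row of the table rests on assumed values, and f = 1 equates a telephone call with a half-hour bedside session, which is an extreme case.
- **That hotline use will go unrecorded.** A contact log is the kind of detail that a full protocol would hold, so its absence from an article shows nothing.

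**Conclusion.** The point holds as a conflict of wording between 3.4 and 3.1 that leaves the control condition open. If control parents use the hotline for CM questions before the three-week questionnaire, and if what they learn acts in the same direction as counseling, the between-cohort differences in information, decision ability and attitudes are biased toward no difference. The size cannot be derived, because the article gives no hotline use. In the assumed range above, the remaining share of the true difference runs from 0.95 to 0.50.

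Recruitment, retention, session completion and acceptability, which carry the main objective and the progression criteria in 4.5, are not affected. The point bears on how the exploratory parent comparison is read. It gives no ground for calling the study invalid.

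**What to change.** Reconcile 3.4 with 3.1 in one sentence: CM counseling content on the hotline follows the same timing as the counseling itself, so for control parents it is available after the three-week questionnaire. Organisational questions and feedback stay open to everyone, and the handling of safety questions is left to the investigators.

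Keep the questionnaire at three weeks in both cohorts. Asking a calling control parent to complete it early would make timing differ by cohort and by interest in CM.

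Record hotline contacts by pseudonym, date and cohort. Report the number of control parents with CM contact before assessment beside the between-cohort results. Do not drop those parents from the comparison: callers are plausibly the parents most interested in CM, and removing them from the control cohort alone would select on behaviour after enrolment.

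The cost is one sentence, a short call log and one reported count. The downside is that some CM answers to control parents wait, as the counseling already does.
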